**Fig. 3 Fig3:**
[figure not shown]
Flowchart for subjects with progressive dyspnea

**Fig. 4 Fig4:**
[figure not shown]
Flowchart for subjects with a moderate or severe exacerbation

## Sample size and statistical analysis

### Sample size calculation

The primary endpoint is the mean difference in ACQ score between the intervention period and the control period whit correction for the baseline ACQ score. This will be tested using a paired t-test for within-subjects designs, with a one-sided alpha of 0.05, a beta of 0.10, a rho of 0.5, a non-inferiority margin of 5% (0.25 ACQ points), an allowable difference (a minimal clinically important difference) of 0.5 ACQ points and a drop-out rate of 10%. The population variance $${\upsigma }_{\mathrm{e }}^{2}$$ was calculated using a real live cohort of patients in the Franciscus Gasthuis & Vlietland. This cohort included all new referrals at the outpatient clinic with a suspicion of asthma. This cohort (n = 52) was selected for having a BMI ≥ 30, blood eosinophils ≤ 0.15 cells/µl, clinically proven asthma, and no obstructive lung diseases otherwise. All patients filled in an ACQ at baseline and 6 months, after which the difference $${ACQ}_{endpoint}- {ACQ}_{baseline}$$ was calculated for every patient. This resulted in a mean of − 0.2749 with a variance 0.7847. A sample size of 120 patients was calculated using the formulae in Fig. 5.

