**Methods:**

The STOP trial is an investigator-initiated, multicenter, non-inferiority, open-label, crossover study aiming to assess whether ICS can be safely withdrawn in adults aged 17–75 years with T2-low asthma and obesity (body mass index (BMI) ≥ 30 kg/m^2^). Patients will be randomly divided into two arms (both n = 60). One arm will start with fixed-dose ICS (control group) and one arm will taper and subsequently stop ICS (intervention group). Patients in the intervention group will remain ICS naïve for ten weeks. After a washout of 4 weeks, patients will crossover to the other study arm. The crossover study takes 36 weeks to complete. Patients will be asked to participate in the extension study, to investigate the long-term metabolic benefits of ICS withdrawal.

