## Methods

### Study design

The STOP trial is initiated by the ‘STZ center of Excellence for Asthma and COPD’ of the Franciscus Gasthuis & Vlietland hospital, collaborating with the Maasstad hospital and the Albert Schweitzer hospital. This multicenter approach ensures a larger number of possible study subjects and decreases selection bias due to social-economical differences between regions of Rotterdam. Patients will be randomized into one of two study groups to avoid allocation bias. Both groups consist of a control period and an intervention period in a 2 × 2 crossover pattern that creates balanced groups maximizes statistical power, and allows for analysing a possible sequence effect. The study has a non-inferiority design, which tests the hypothesis that ICS tapering is not inferior to ICS continuation. This intervention trial has an open-label to determine the effects of ICS tapering in a real-life situation.

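### The primary paired t-test has no period term: if ACQ change differs between the two periods, the interval is too wide and, with unequal completion of the sequences, the estimate is biased

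*Protocol article*

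**What the plan says.** Under Sample size calculation, the primary endpoint is the baseline-corrected mean ACQ difference between the intervention and control periods, and "This will be tested using a paired t-test for within-subjects designs". The planning values are given "with a one-sided alpha of 0.05, a beta of 0.10, a rho of 0.5", with a margin of 0.25 ACQ points and 10% dropout. The variance comes from a referral cohort (n = 52) followed for 6 months: "This resulted in a mean of − 0.2749 with a variance 0.7847".

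Under Statistical analysis, baseline and endpoint ACQ are taken separately in each period. Non-inferiority is judged from a one-sided 95% interval for the mean difference, and no period or sequence term is mentioned. Linear mixed models are named only for secondary parameters.

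Under Study design, the crossover layout is said to be one that "allows for analysing a possible sequence effect". Under Study procedures the second baseline is given the same purpose. Neither remark is tied to the primary test.

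**The concern.** A paired t-test on a 2 × 2 crossover pools the intervention-minus-control differences as if all patients had taken the treatments in the same order. Any difference between the periods enters those differences with one sign in sequence Intervention-Control (I-C) and the opposite sign in sequence Control-Intervention (C-I). If both sequences complete in equal numbers, it cancels from the mean but stays in the estimated variance. If they do not, part of the period difference is counted as treatment effect.

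The margin is only 0.25 points, so a few hundredths of a point affect the decision. Unequal completion is possible: patients leave after a second moderate or severe exacerbation or by choice, and I-C patients undergo withdrawal first and must then stay for the whole second period.

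**Working it through.** **Inputs from the protocol article:** one-sided alpha 0.05, power 0.90, rho 0.5, margin 0.25, variance 0.7847, dropout 10%, 60 patients per sequence.

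**Assumed, because the article gives neither:** the period effect π (mean ACQ change in period 1 minus that in period 2), 0 to 0.4 in size; and the split of completers by sequence.

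**1. The planned size.** Variance of the paired difference = 2 × 0.7847 × (1 − 0.5) = 0.7847. Evaluable n = (1.645 + 1.282)² × 0.7847 / 0.25² = 107.5, rounded up to 108. Then 108/0.9 = 120. The stated 120 is reproduced with no period effect and a true difference of zero.

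**2. Where a period effect enters.** With true effect τ, the expected intervention-minus-control difference is τ + π in I-C and τ − π in C-I. Hence
- bias of the pooled mean = π × (n_IC − n_CI)/N;
- expected variance estimate ≈ 0.7847 + π² when the sequences are balanced;
- true sampling variance of the mean = 0.7847/N, unchanged, because π is fixed within a sequence.

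**3. Which time trends count.** The endpoint is change from a period-specific baseline. The intervals are equal whether read as weeks 4 to 18 and 22 to 36, or as weeks 0 to 18 and 18 to 36. A level shift or a steady linear drift therefore gives π = 0. Only a difference between the periods in the change itself matters, such as improvement after trial entry that is concentrated in period 1.

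**4. Balanced completers, 54/54.** True standard error = √(0.7847/108) = 0.0852; t(0.95, 107) = 1.659. Power ≈ Φ[(0.25 − 1.659 × estimated SE)/0.0852].
- π = 0: (0.25 − 0.1414)/0.0852 = 1.27, power 0.90.
- |π| = 0.2749: estimated variance about 0.861, SE 0.0893; (0.25 − 0.1481)/0.0852 = 1.20, power 0.88. The interval is about 5% wider than it need be (√(0.861/0.7847) = 1.047).
- |π| = 0.40: estimated variance about 0.946, SE 0.0936; (0.25 − 0.1553)/0.0852 = 1.11, power 0.87. The interval is about 10% wider (√(0.946/0.7847) = 1.098).

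Bias is zero throughout. Simulated one-sided type I error is about 0.042 at |π| = 0.2749, so the test is conservative.

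**5. Worst case, all 12 dropouts in I-C (48/60).** Bias = π × (48 − 60)/108 = −0.111π. At |π| = 0.2749 this is 0.031 points in size, and 0.031/0.25 = 12% of the margin. Simulated results:

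| Completers I-C/C-I | π | Paired t-test: power | Paired t-test: type I error | With period term: power | With period term: type I error |
|---|---|---|---|---|---|
| 54/54 | ±0.2749 | 0.88 | 0.042 | 0.90 | 0.05 |
| 48/60 | +0.2749 | 0.94 | 0.086 | 0.89 | 0.05 |
| 48/60 | −0.2749 | 0.80 | 0.02 | 0.89 | 0.05 |

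Positive π means that patients do worse in period 1. With I-C the depleted sequence, the bias then favours withdrawal. Negative π (more improvement in period 1) biases against it. If C-I loses the patients, the signs reverse.

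At a milder 51/57 the bias halves: 0.2749 × 6/108 = 0.015. Simulated type I error is then about 0.06, or power about 0.84.

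**The case against.** Four points deserve weight.

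- **The period-specific baselines already remove much of the problem.** This stands. A reader might infer that any time trend damages the primary test; the endpoint definition does not support that, because level shifts and steady linear drift cancel.
- **The cohort's change does not show that a period effect will occur.** This stands too. Since 0.2749 exceeds the 0.25 margin, one might infer that a period effect of about that size is to be expected, or scale it to the time between the two endpoints. But it is a single 6-month mean change in newly referred patients. It says nothing about whether change differs between the trial's two periods, and under linear drift the period effect would be zero. I use it only as an illustrative size.
- **The bias needs two conditions together.** Correct. It takes both a period effect and unequal completion, and 48/60 puts the whole planned dropout in one sequence. Both sequences undergo withdrawal, so C-I also has exits, in period 2. With balanced completion, the wider standard error makes the test conservative; it does not raise type I error.
- **The model may be specified in an unseen analysis plan.** This stands in part. The test is named in the sample size section, and an article condenses. But it names a specific test for the decisive comparison and mentions mixed models only for secondary parameters, so the stated choice can be judged as written.

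**Conclusion.** The point holds in a limited form and is a free improvement, not a flaw that invalidates the design. As stated, the primary test ignores period. With balanced completers the consequence is small: no bias, slight conservatism, and power of about 0.88 at |π| = 0.27 or 0.87 at 0.40 instead of 0.90. With a period effect and unequal completion together, the estimate is biased. The worst case examined (48/60, |π| = 0.27) gives 0.03 points, with type I error of about 0.086 or power of about 0.80 according to the sign of π.

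These figures rest on an assumed period effect and assumed completion patterns. The formulas and the reproduction of 120 rest on the article's own inputs.

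**What to change.** Name the primary analysis as a crossover model for the period-level ACQ change, with treatment and period as fixed effects and patient as random effect. For patients with both periods, this is equivalent to averaging the two sequence-specific mean differences. Base the decision on the upper one-sided 95% limit for intervention minus control, since a higher ACQ is worse, and compare it with 0.25. State that this replaces the unadjusted paired t-test and that the announced sequence analysis is separate from it.

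The cost is one degree of freedom and a change of wording. In the scenarios tabulated under the check, the adjusted estimate keeps type I error at about 0.05 and power at about 0.89 to 0.90, so N = 120 need not change.

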After completing the first period, patients will crossover from the intervention arm to the control arm and vice versa. There is a-4 week washout/run-in period between the first and second periods to avoid carry-over effects. A second baseline ensures analysis of sequence effects. After completion of the second intervention period, intervention- and control data will be compared. The trial results will be shared with the participants and other relevant parties during a ‘patient participation meeting’.

This design is powered on demonstrating sustained asthma control, with a limitation in terms of measuring long-term health benefits (e.g. metabolic alterations) of ICS tapering. To study the long-term effects of ICS withdrawal in T2-low asthma patients with obesity, we will extend the study by 2 years in an open-label extension study. In this extension study, patients will remain ICS naïve. Patients may only participate in the extension study after successful discontinuation of ICS in the crossover period.

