### Statistical analysis

Study data will be analysed according to the intention-to-treat approach. Results of the statistical analysis consist of descriptive univariable and multivariable analysis. Continuous parameters with (approximately) normal distributions will be summarized with means and SDs (or 95% CIs). Continuous primary study parameters with skewed distributions will be summarized with medians and interquartile ranges (IQR). Finally, nominal and ordinal primary study parameters will be summarized with numbers (percentages).**Primary study parameter**

The primary endpoint is defined as the difference in ACQ between the intervention period and control period relative to the baseline ACQ score. Definitions:Baseline: ACQ score at the first visit of period 1 or period 2Endpoint: ACQ at last visit of period 1 or period 2

The non-inferiority margin is 5% (i.e., 0.25 out of a maximum of 5 ACQ points). Non-inferiority will be established if the lower limit of a one-sided 95% confidence interval for the mean difference in ACQ score between the intervention period and control period is within the absolute 5% non-inferiority margin of the mean in the control arm.2.Secondary study parameter(s)

The time to first exacerbation will be tested with Kaplan–Meier curves and log-rank tests to estimate the effect over time for both patient groups. Next, Cox regression will be used to measure the treatment effect adjusted for BMI and hospital as fixed covariates.

The majority of secondary variables are continuous and will be described by descriptive compared between intervention group and control group.

The change in time of several secondary parameters will be estimated by repeated measurements analysis. Linear mixed modeling will be used for continuous variables. Generalized estimated equations for binary data with logit link function will be used for the categorical variables.3.Interim analysis

No interim analysis has been planned to prevent alpha loss. An independent Data Safety Monitoring Board (DSMB) may conduct an investigation of adverse events when ≥ 12 exacerbations may have occurred.

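### The 90% power needs a correlation of 0.5 between changes from separate period baselines; the plan gives no support for it, and about 65% to 84% is more plausible

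*Protocol article*

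**What the plan says.** All references are to the protocol article.

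- **Test.** In Sample size calculation: "This will be tested using a paired t-test for within-subjects designs".
- **Error rates and correlation.** "with a one-sided alpha of 0.05, a beta of 0.10, a rho of 0.5". No source is given for rho, and the text does not say which two quantities it correlates. The formulae are in Fig. 5, which is not shown.
- **Margin and drop-out.** "a non-inferiority margin of 5% (0.25 ACQ points"), and "a drop-out rate of 10"%.
- **Variance.** In a clinic cohort of 52 patients, the change in ACQ from baseline to 6 months was computed for each patient: "This resulted in a mean of − 0.2749 with a variance 0.7847".
- **Endpoint.** In Statistical analysis: "difference in ACQ between the intervention period and control period relative to the baseline ACQ score". That section takes the baseline from the first visit of each period and the endpoint from its last visit.
- **Second baseline.** In Study procedures: "A second baseline ensures analysis of sequence effects". Table 1 labels weeks 4 and 22 as the baseline visits; the periods end at weeks 18 and 36.

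**The concern.** A paired t-test has no covariates. If it is to correct for baseline, the baseline must be subtracted. The contrast is then (endpoint minus baseline) on intervention, minus (endpoint minus baseline) on control, with a different baseline in each half.

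Two scores from one patient are usually positively correlated because the patient has a stable level of asthma control. Each change has already had that level removed. What remains is visit-to-visit noise from four separate measurements, and nothing in the article suggests that the two changes share half of their variance. A correlation of 0.5 arises naturally, under equal correlation, when both changes use one common baseline. That baseline would cancel from the contrast anyway, and the article does not define it so.

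At stake is the chance that a neutral withdrawal fails to show non-inferiority. The plan puts it at one in ten; under equal correlation it is about one in three. The Discussion says that failed tapering would count in favour of continued ICS exposure, so a false failure would be given a clinical reading.

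**Working it through.** **Inputs (Sample size calculation):** change-score variance v = 0.7847, margin 0.25, one-sided alpha 0.05, power 0.90, rho = 0.5, drop-out 10%. The true difference is taken as 0.

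**1. The plan's own figure.** For a paired difference, Var(D) = 2v(1 − rho) = 2 × 0.7847 × 0.5 = 0.7847.

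n = Var(D) × (1.645 + 1.282)² / 0.25² = 107.5, so 108 evaluable; 108 / 0.9 = 120. The stated 120 is reproduced. Power at 108 is 90.1% by the normal approximation and 89.8% by the noncentral t. With rho = 0 the same normal formula gives 216 evaluable and 240 enrolled, so the planned size depends on rho.

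**2. The correlation implied by the endpoint.** Write each ACQ score as a patient level plus independent visit noise with variance s² (equal correlation between all visits).

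- Each change has variance 2s², so 2s² = 0.7847.
- The two changes share no visit and the patient level has cancelled, so their covariance is 0 and rho = 0.
- Var(D) = 4s² = 2 × 0.7847 = 1.5694, twice the planned value.

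The same doubling follows if 0.5 was meant as the correlation between raw scores.

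**3. Power by rho, variance per change held at 0.7847, 108 evaluable (noncentral t).**

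| rho | Var(D) | Power |
|---|---|---|
| 0.5 | 0.785 | 90% |
| 0.25 | 1.177 | 77% |
| 0 | 1.569 | 66% |

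At rho = 0, 90% power needs 217 evaluable by the noncentral t; 217 / 0.9 = 241.1, so about 241 to 242 enrolled.

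**4. Serial correlation.** Suppose the correlation between visits k weeks apart is r^k, with total variance T. The cohort's variance is for a six-month change, so T is set by 2T(1 − r²⁶) = 0.7847. With visits at weeks 4, 18, 22 and 36:

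Var(D) = T × [4 + 2(r⁴ + r³² − 2r¹⁴ − 2r¹⁸)].

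| Weekly r | T | Var(D) | Power at 108 |
|---|---|---|---|
| 0.90 | 0.420 | 1.62 | 65% |
| 0.95 | 0.533 | 1.32 | 73% |
| 0.97 | 0.717 | 1.15 | 78% |
| 0.99 | 1.706 | 0.95 | 84% |

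The changes are negatively correlated here (−0.25 to −0.06), but a 14-week change also varies less than a 26-week change, which recovers part of the loss. The range of r is an assumption.

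**5. What rho = 0.5 would require.** Patient-specific trends that repeat in both periods, on and off ICS, would have to make up half of the change variance: 0.5 × 0.7847 = 0.39, a standard deviation of 0.63 ACQ points. That is more than the 0.5 points that the article takes as clinically important.

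**6. Without subtraction.** Under equal correlation the difference between the two end-of-period scores has variance 2s² = 0.7847, so power at 108 evaluable is again about 90%. Adding the period baselines as covariates leaves this essentially unchanged. Under the serial model of step 4 it is above 90%. If 0.7847 is instead taken as the variance of a 14-week change, it is about 84% to 88%.

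**The case against.** Four arguments deserve weight.

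- **The meaning of rho is inferred.** Fig. 5 is not shown. Because 2(1 − 0.5) = 1, the figure of 120 also follows if 0.7847 was used directly as the variance of a within-patient difference between two ACQ scores. This stands: the arithmetic does not show what the authors had in mind. It does not rescue the stated power for the endpoint as defined, which involves four scores.
- **Some positive correlation could remain.** If patients drift alike after each run-in, rho exceeds 0. This also stands, and is why a range is given. Step 5 shows how large the drift would have to be to reach 0.5.
- **Covariate adjustment is not excluded.** The paired t-test is named only in the sample size paragraph, and the analysis section names no test for the primary endpoint. That is fair, but the test, the change-score variance and the period-specific baselines together point to subtraction, and no other method is stated for this endpoint.
- **Bias and type I error are untouched.** Correct; this is a matter of power and of a clear primary analysis.

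A reader might infer that the trial's power simply is 66%, or is below 60%. The documents support neither. The first rests on equal correlation, which is assumed. The second combines a negative rho (59% at rho = −0.2) with the six-month variance left unchanged for 14-week changes; if nearer visits are more alike, that variance must fall too, and step 4 then gives 65% to 84%.

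**Conclusion.** The concern holds as a matter of unsupported power, not as a single corrected figure. The paired test, the baseline correction, the separate baseline for each period and the change-score variance describe a difference of two changes, and rho = 0.5 between such changes has no basis in the article. For 108 evaluable patients and no true difference, power is about 66% under equal within-patient correlation, about 65% to 84% under serial correlation calibrated to six months, 77% at rho = 0.25, and 90% only at rho = 0.5. These figures assume that the cohort variance carries over to the trial; the correlation structures are assumptions, since the article reports no visit-to-visit correlations.

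**What to change.** Make the primary analysis a linear mixed model of end-of-period ACQ-5 (weeks 18 and 36), with treatment and period as fixed effects, patient as random effect, and the two period baselines (weeks 4 and 22, as labelled in Table 1) as covariates, not subtracted. Say explicitly that these are the baseline visits, because Table 1 also lists week 18 as the run-in visit of period 2. State which quantities rho correlates.

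This changes only the wording of the analysis. It needs no further patients, visits or data, and keeps about 90% power with 120 enrolled under equal correlation.

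If change scores are kept, restate the power as the range above with the assumption behind each figure. Under equal correlation, 90% power would then need about 217 evaluable patients, or about 241 to 242 enrolled.

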**Fig. 5 Fig5:**
[figure not shown]
Formulae used in sample size calculation

### Statistical analysis

Study data will be analysed according to the intention-to-treat approach. Results of the statistical analysis consist of descriptive univariable and multivariable analysis. Continuous parameters with (approximately) normal distributions will be summarized with means and SDs (or 95% CIs). Continuous primary study parameters with skewed distributions will be summarized with medians and interquartile ranges (IQR). Finally, nominal and ordinal primary study parameters will be summarized with numbers (percentages).**Primary study parameter**

The primary endpoint is defined as the difference in ACQ between the intervention period and control period relative to the baseline ACQ score. Definitions:Baseline: ACQ score at the first visit of period 1 or period 2Endpoint: ACQ at last visit of period 1 or period 2

The non-inferiority margin is 5% (i.e., 0.25 out of a maximum of 5 ACQ points). Non-inferiority will be established if the lower limit of a one-sided 95% confidence interval for the mean difference in ACQ score between the intervention period and control period is within the absolute 5% non-inferiority margin of the mean in the control arm.2.Secondary study parameter(s)

The time to first exacerbation will be tested with Kaplan–Meier curves and log-rank tests to estimate the effect over time for both patient groups. Next, Cox regression will be used to measure the treatment effect adjusted for BMI and hospital as fixed covariates.

The majority of secondary variables are continuous and will be described by descriptive compared between intervention group and control group.

The change in time of several secondary parameters will be estimated by repeated measurements analysis. Linear mixed modeling will be used for continuous variables. Generalized estimated equations for binary data with logit link function will be used for the categorical variables.3.Interim analysis

No interim analysis has been planned to prevent alpha loss. An independent Data Safety Monitoring Board (DSMB) may conduct an investigation of adverse events when ≥ 12 exacerbations may have occurred.

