**Questionnaires**
**ACQ-5:** In this study the ACQ-5 will be used, consisting of five patient self-reported questions. The recall time is one week with a score range of 0 to 6 (0 = never and 6 = always). A higher score is associated with worse asthma control. The minimal clinically important difference of the ACQ is 0.5 [23].**AQLQ:** The AQLQ consists of 32 items with a 3 week recall period. The score range per question is 1 to 7 (1 = severely impaired and 7 = not impaired at all). It is used to qualify the disease-specific health-related quality of life [24–26].**MRC:** The MRC (Medical Research Council) is a dyspnea scale, as a measure of disability in patients with respiratory disabilities. It consists of one question about the shortness of breath and six possible answers. The score range per question is 0 to 5 (0 = no shortness of breath at all and 5 = too breathless to leave the house). A higher score is therefore associated with a high burden of disease [27].**FSS:** The FSS (Fatigue Severity Scale) measures fatigue severity. It has 9 items with are scored on a 7 point Likert scale. A higher score is associated with higher fatigue severity [28].

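### The 0.25-point non-inferiority margin is wrongly expressed as 5% of a 5-point scale, and the decision sentence gives no points value and can be read as 5% of the control mean

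*Protocol article*

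**What the plan says.** The margin appears in two sections of the protocol article.

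- **Sample size calculation:** "a non-inferiority margin of 5% (0.25 ACQ points", to be tested "with a one-sided alpha of 0.05". The same list contains "an allowable difference (a minimal clinically important difference) of 0.5 ACQ points".
- **Statistical analysis, primary study parameter:** "The non-inferiority margin is 5% (i.e., 0.25 out of a maximum of 5 ACQ points". The decision rule follows: "Non-inferiority will be established if the lower limit of a one-sided 95% confidence interval" for the mean ACQ difference between the periods "is within the absolute 5% non-inferiority margin of the mean in the control arm".

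The Questionnaires section describes the instrument: "The recall time is one week with a score range of 0 to 6". It adds that higher scores mean worse control and that the minimal clinically important difference (MCID) is 0.5.

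**The concern.** Two things in the primary decision rule do not fit together.

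1. **The percentage has the wrong base.** A 5-point maximum contradicts the 0-6 range given elsewhere in the same article. A reader who trusts the percentage and the published range obtains 0.30. A reader who trusts the points value obtains 0.25.
2. **The operative sentence names no number of points.** It gives a percentage and then mentions the control-arm mean. Taken literally, that could be a relative margin whose size is known only once the control data are in.

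Two neighbouring details add to the uncertainty. The 0.5 figure stands beside the margin with no stated role. The rule also uses a lower confidence limit without saying which period is subtracted from which, although a higher score is worse.

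In a non-inferiority trial the margin decides the conclusion. If the text supports more than one threshold, the same result can be reported as success or as failure. The article's Discussion expects the outcome to influence guidelines.

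**Working it through.** **Inputs.** From Sample size calculation: one-sided alpha 0.05, beta 0.10, rho 0.5, variance of ACQ change 0.7847, margin 0.25, drop-out 10%, N = 120. From Questionnaires: range 0 to 6. The article gives no control-period mean, so values of 1, 2 and 3 are assumed below.

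**Step 1: reproduce N.**

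- Variance of the paired difference: 2 × 0.7847 × (1 − 0.5) = 0.7847.
- n = (z0.95 + z0.90)² × variance / distance² = (1.645 + 1.282)² × 0.7847 / 0.25² = 107.5, rounded up to 108 pairs.
- Drop-out: 108 / 0.9 = 120. This matches the stated figure.

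A distance of 0.30 gives 75 pairs (84 with drop-out), and 0.50 gives 27 pairs (30 with drop-out). The trial was therefore sized on a distance of 0.25. N does not show how that distance arose: 0.25 − 0 and 0.5 − 0.25 are both 0.25.

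**Step 2: check the percentage.**

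- 0.05 × 5 = 0.25, but 0.05 × 6 = 0.30.
- 0.25 / 6 = 4.2%.
- 5% of a control mean equals 0.25 only if that mean is 0.25 / 0.05 = 5.0.

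**Step 3: precision at the planned size.** With 108 completers, SE = √(0.7847 / 108) = 0.0852. The one-sided 95% half-width is 1.645 × 0.0852 = 0.140.

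**Step 4: what each reading would do.** The difference is intervention minus control, compared through its upper limit. The largest observed difference that passes is the margin minus 0.140. Power at a true difference of 0 is Φ(margin / 0.0852 − 1.645).

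| Reading | Margin | Largest passing difference | Power |
|---|---|---|---|
| Stated points value | 0.25 | 0.110 | 90% |
| 5% of the 0-6 maximum | 0.30 | 0.160 | 97% |
| 5% of control mean 1 (assumed) | 0.05 | −0.090 | 14% |
| 5% of control mean 2 (assumed) | 0.10 | −0.040 | 32% |
| 5% of control mean 3 (assumed) | 0.15 | 0.010 | 55% |

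**Step 5: results on which the readings disagree.**

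- Observed difference 0.12: upper limit 0.12 + 0.14 = 0.26. It fails at 0.25 and passes at 0.30.
- Observed difference 0.05: upper limit 0.05 + 0.14 = 0.19. It passes at 0.25 and fails at 5% of any control mean below 0.19 / 0.05 = 3.8.

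**Step 6: the confidence limit.** If the difference is intervention minus control, the stated lower limit looks in the wrong direction. An observed worsening of 0.35 has a lower limit of 0.35 − 0.14 = 0.21, which would pass at 0.25. The lower limit is the right one only for control minus intervention, where it must lie above −0.25.

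**The case against.** The strongest reply is that the protocol contains one numerical margin, not several. The value of 0.25 points is stated in both statistical sections and reproduces N = 120 exactly. The sentence just before the decision rule defines the 5% as 0.25 points, and the rule calls the margin absolute. Read together, the natural meaning is within 0.25 points of the control mean. On this view the 5-point maximum is a slip in a gloss, and nothing suggests that 0.30 would be applied.

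Most of that stands, and it limits the point in three ways.

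- **The 0.5 is not a rival margin.** A reader might infer that the threshold could be 0.50, or that a true worsening of 0.5 was assumed, which would lie outside a 0.25 margin. The protocol labels 0.5 as the MCID, lists it separately and never calls it the margin. Its role in the calculation may be clear from the formulae in Fig. 5, which could not be consulted here.
- **A relative margin is the less natural reading.** A reader might infer that the protocol fixes a data-dependent margin, or leaves the choice until the control mean is known. The word absolute points the other way. The low power figures under that reading rest on control means that the article does not supply.
- **The sample size is not wrong** for a margin of 0.25.

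The reply does not remove the contradiction between a 5-point maximum and a 0-6 range. Nor does it put a points value into the sentence that decides the trial. An absolute 5% still needs a base, and the only base given conflicts with the instrument's range.

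**Conclusion.** The point holds in a limited form. The intended margin is 0.25 ACQ points, and the trial was sized on that distance. Its percentage form is wrong on the protocol's own scale (4.2%, not 5%; 5% would be 0.30). The decision sentence omits the points value and attaches the percentage to the control-arm mean, so it can be misread.

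At the planned precision, observed differences between about 0.11 and 0.16 change verdict between 0.25 and 0.30. Under the less likely relative reading the margin would be only 0.05 to 0.15 for assumed control means of 1 to 3. These figures assume 108 completers, a paired-difference variance of 0.7847 and a normal approximation.

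The documents do not support a claim that four margins compete, that 0.5 is one of them, or that N = 120 is in error. They also do not establish which true difference was assumed. A value of 0 fits, but N alone cannot confirm it.

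**What to change.** Make these changes in the two statistical sections:

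1. State one margin, in the same words in both places: 0.25 points, absolute, on the 0-6 ACQ-5 scale. Delete the percentage, the reference to a 5-point maximum and the reference to the control-arm mean.
2. Rewrite the decision rule with its direction. For example: *withdrawal is non-inferior if the upper limit of the one-sided 95% confidence interval for the mean baseline-corrected ACQ-5 difference, intervention minus control, is below 0.25 points.*
3. In Sample size calculation, label 0.5 as the MCID and not as a margin. State the true difference that was actually assumed. A value of 0 reproduces N = 120, but it should be confirmed against the formulae in Fig. 5 before it is written in.

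The cost is wording only. The margin stays at 0.25 and N stays at 120. The change should be made and dated before the primary comparison is run.
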